**Behavioural Activation for depressive symptoms in young people with emerging or early psychosis: A pilot study protocol**

**Introduction**

Psychosis is commonly characterized by the misinterpretation of or difficulties in accurately perceiving reality [1]. The symptoms of psychosis often emerge in young people, where in 80% of cases the first episodes of psychosis occur sometime between the late teenage years and 30 years of age [2]. Early intervention for people experiencing a first episode of psychosis (FEP) is essential to improve functioning, promote recovery, and prevent future episodes [3]. More recently, there has been recognition that providing treatment earlier than during that first episode can be of benefit for individuals who are at ‘ultra high risk’ (UHR) of developing psychosis. This time where sub-threshold symptoms are experienced, is also referred to as “emerging psychosis”, “at-risk-mental-state” or “clinical high-risk” [4].

While treatment for an individual’s FEP often results in remission of psychotic symptoms, co-morbid psychiatric diagnoses are common. One of the most common among young people with emerging or early psychosis (YPEEP) is depressive symptoms occurring in up to 75% of the YPEEP population [5]. Co-occurring depression is associated with poor outcomes, including a 59% increase in suicidal behaviour [6], a higher frequency of hospital admissions [7] and a reduction in occupational and social functioning [8]. Depressive symptoms may also have a role in progressing the psychosis prodrome [9, 10] and improvements in depressive symptoms are associated with reductions in psychotic-type symptoms in young people [11]. There is clear evidence that Cognitive Behavioural Therapy (CBT) can be effective at treating depression in YPEEP [12-14]. However, CBT is a complex/expensive intervention requiring clinicians to undergo specialist training and deliver complex treatment protocols [12]. Hence, it is essential to establish easily accessible, safe and effective psychosocial treatments for depression in YPEEP.

Evidence from meta-analyses has shown Behavioural Activation (BA) therapy to be as effective at treating depressive symptoms as CBT in the general population [15-17]. Furthermore, a systematic review and meta-analysis has reported the promising effect, feasibility, and acceptability of BA specifically in the treatment of depression among young people [18]. Theoretically, BA may also help YPEEP experiencing depression, assisting them to reconnect with positive experiences by using activity monitoring and goal-led activity scheduling [15]. Importantly, BA is an intervention that can be delivered with high levels of fidelity by non-specialist clinicians and requires minimal training [17, 19], which would be of particular benefit in areas with a lack of psychologists and other staff with specialist training.

To the best of our knowledge there has been no previous trial evaluating the acceptability and feasibility of BA interventions for a YPEEP population. This project would be the first to establish the feasibility of clinician delivered BA as an adjunct to standard care to reduce depression in YPEEP. These novel findings will inform the design of a full, appropriately powered randomized controlled trial.

**Study aim and objectives**

The overall aim will be to train at least eight clinicians in BA using an established University accredited online “Professional Certificate in BA for Depression” program and support them to deliver BA to improve depressive symptoms in YPEEP. Specifically, the objectives of the pilot trial are to:

1. Establish the proportion of YPEEP with clinically meaningful depression symptoms.
2. Establish the proportion of clinicians that complete the BA training and are deemed to be competent.
3. Determine the proportion of eligible participants approached who agree to consent to the research.
4. Determine the proportion of participants that complete baseline measures, complete BA treatment (attending for a minimum of six sessions over the six weeks), and complete follow-up measures (immediately post intervention and at 3 months follow-up).

Additionally, we will:

1. Establish clinicians’ fidelity to treatment.
2. Calculate preliminary efficacy of BA on clinical outcome measures.
3. Explore participants’ experiences of facilitating BA (clinicians) and receiving BA (YPEEP).

**Materials and methods**

**Study design**

The feasibility and acceptability of delivering BA to YPEEP clients will be assessed using a pilot controlled clinical trial with a two-arm parallel-group design. This pilot trial protocol is registered with the Australian New Zealand Clinical Trials Registry (ref no. ACTRN12622000756729). The ‘Standard Protocol Items: Recommendations for Interventional Trials’ (SPIRIT) [20, 21] is used to guide the presentation of the current study protocol (see S1 File: Completed SPIRIT checklist). The pilot trial will be conducted in accordance with IHI Good Clinical Practice guidelines. A trial steering committee will be convened to oversee and guide the research as needed.

**Study setting**

This study will be carried out in a youth early psychosis service in Australia between June 2022 and October 2023 known as *headspace* Early Psychosis (hEP) [22]. The early psychosis service is one of the services offered by a youth mental health centre providing mental health services to young people aged 12-25. The early psychosis service had 102 YPEEP clients receiving treatment in the first quarter of 2021 and receive an average of 12 new referrals each month. Additional hEP treatment centres will be recruited where necessary.

**Participants**

*Inclusion criteria for clinicians*

Any clinician with at least 6 months of experience of working with young people with early or emerging psychosis, who is working with clients at the early psychosis service will be eligible to take part. Examples of clinician who may work in these roles include, but are not limited to; registered nurses, social workers, youth peer support workers, occupational therapists, psychologists and psychiatrists.

*Inclusion criteria for YPEEP clients*

Clients aged 15 years and older who are engaged with the early psychosis service will be eligible to participate if they:

1. have experienced early/emerging psychosis (<5 years), received ≥1 month of care, and are experiencing depressive symptoms [BPRS depression item score ≥3, according to the most recent BPRS assessment conducted by clinical staff within routine clinical practice];
2. are able to understand and speak English; and
3. are able to provide informed consent.

Clients will be excluded if they have a primary diagnosis of substance misuse (i.e. that the psychosis or UHR state is secondary to substance misuse disorder), express suicidal ideation or present a known risk to themselves/others.

**Sample size**

There has been some degree of ambiguity about sample size requirements for feasibility studies and there are no previous studies which have evaluated BA in YPEEP which could be used to guide this estimate. Therefore, our sample size estimation will be based on recommendations from the literature that feasibility studies ought to aim for sample sizes of between 24 and 50 participants [23, 24]. Furthermore, a systematic review of UK registered feasibility studies reported the median sample size with continuous outcome measures to be 30 participants per group [25]. Based on this guidance, our target sample size is 60 participants (30 in each group). This estimate will facilitate the generation of information about sample size requirements for a subsequent full-scale trial and is not intended to be sufficiently powered to detect statistically significant differences in outcomes between groups.

**Recruitment**

An information sheet about the research will be provided to and discussed with eligible clinicians who are staff members working in the early psychosis service. For the clinicians who are willing to participate, they will be asked to review the informed consent form and confirm their agreement to participate by signing this form. Potential YPEEP participants will be initially identified by clinicians, who will determine whether the young person meets the study inclusion criteria.

Potential YPEEP participants will be briefly informed about the study by their clinician and offered a study flyer containing more detailed information. If the young person is interested in taking part, they will be asked for their permission to be approached by a trained research assistant. If permission is granted, the research assistant will then provide each potential participant with a detailed study information sheet. The research assistant can offer further explanation or clarification and address any questions or concerns potential participants may have, as needed. Potential participants will be encouraged to discuss the study with their families and other appropriate people and will be given adequate time (at least 48 hours) to consider the invitation. Eligible young people who are 18 years of age and older and wish to participate, will be asked to review the informed consent form and confirm their agreement to participate by signing this form. If the eligible young person wishing to participate is less than 18 years of age, consent will be sought from their parent/guardian, in addition to obtaining the informed consent of the young person. Recruitment will cease when the planned sample size is reached.

At the conclusion of the intervention, the researchers will invite a subsample of clinicians and YPEEP participants to take part in a semi-structured interview. Clinicians and YPEEP participants will be advised on their respective information sheets and informed consent forms that they can participate in the trial and later decide not to participate in an interview. A purposive sample of a minimum 4 clinicians and 12 YPEEP participants will be interviewed 3-months post intervention (additional interviews may be conducted until data saturation is met). YPEEP participants will be purposively sampled to capture the range and diversity of experiences; based on their attendance at the BA sessions, engagement with the trial more generally and clinical outcomes. A member of the research team will contact selected clinicians and YPEEP participants and invite them to be interviewed. Consent to participate in the interview will be reconfirmed prior to arranging the interview and potential interviewees will be reminded of their rights in the study.

**Random treatment allocation and blinding**

Baseline data will be collected from YPEEP participants who will then be randomly assigned into either: 1) the BA group, who will receive BA therapy in addition to TAU or 2) the TAU group, who will receive the standard care currently offered by the service. Random treatment allocation will be generated by an external computerized randomization service which uses block randomization with random permuted block sizes to ensure appropriate allocation concealment and equal samples across groups. The external randomisation service will hold the allocation sequence and inform the trial coordinator of participants’ group allocation via text message once baseline data has been collected from consenting participants. The trial coordinator then will inform the participant and clinician of treatment allocation. Allocation will be blinded to the statistician, but it will not be masked to the clinicians and research assistants who will collect baseline, post-intervention, and follow-up outcome data.

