**Preliminary intervention effects (primary and secondary outcomes)**

The primary outcome will be the assessment of depressive symptoms. The secondary outcome will be the assessment of negative symptoms, overall psychiatric symptoms, medication side effects, and functioning. Outcome measures will be completed at baseline (0 weeks), immediately post-intervention (6 weeks) and 3-months post-intervention.

Depressive symptoms: The depressive symptoms will be measured with Calgary Depression Scale for Schizophrenia (CDSS) [30]. The CDSS is a 4-point Likert type scale (0, absent; 1, mild; 2, moderate; 3, severe) with nine items. It is considered to be a reliable scale, with high internal consistency (Cronbach's alpha= 0.855), and the CDSS is suitable for evaluating symptoms of depression in people at clinical high risk for psychosis [31], including young people [32].

Negative symptoms: The Scale for Assessment of Negative Symptoms (SANS) [33] will be used to assess the negative symptoms of schizophrenia. SANS is 6-point Likert type scale (from 0, none to 5, severe), comprised of five scales each of which assess aspects of negative symptoms; alogia, affective blunting, avolition-apathy, anhedonia-asociality, and attentional impairment. The SANS has demonstrated a high level of reliability, with an overall Cronbach’s alpha ranging from 0.89 to 0.95 and global intraclass correlation coefficient (test-retest reliability) of more than 0.82 in different studies [33-35].

Psychiatric symptoms: The Brief Psychiatric Rating Scale (BPRS) [36] is a 7-point Likert type scale (1, not present-7, extremely severe) which is used to rate psychiatric symptoms such as anxiety, depression, and psychoses. The BPRS has demonstrated good reliability, with overall Cronbach’s alpha value of 0.69 [37] and an overall intra-class correlation of R = 0.78 (p< 0.001) [38].

Medication side effects: The Glasgow Antipsychotic Side-effect Scale (GASS) [39] is 4-point Likert type scale (from 0 point, never to 3 point, everyday) containing 22 items. It is a self-report rating scale which measures an individual’s viewpoint about side effects of antipsychotic medication. The GASS has demonstrated a good test-retest reliability (kappa value=0.72) [39] and internal consistency reliability with Cronbach's alpha ranging from 0.793 to 0.903 [40-42].

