**Data collection and management**

The trained research assistant will facilitate the data collection process. With prior written consent, participant demographic information will be collected through the early psychosis service at the study site. For the primary (depressive symptoms) and secondary outcomes (negative symptoms, overall psychiatric symptoms, medication side effects, functioning), the data will be collected at baseline, 6 weeks post-intervention and 3 months post-intervention respectively. There are no plans for specific activities to promote participant retention other than the BA intervention being facilitated by participants’ regular clinician and by keeping participant burden to a minimum. With participants’ permission, all outcome data will be collected and analysed from participants who discontinue the study or deviate from the intervention protocol.

The qualitative interviews will be audio-recorded and will subsequently be transcribed. The researcher conducting the interview will ensure that there is no patient identifiable information (e.g. names, addresses) on the audio recording. A professional transcription service with appropriate confidentiality and data security policies will be engaged to transcribe digital recordings of the interviews. Transcriptions will be de-identified by the research team to ensure anonymity. Subsequently, audio-recordings will be securely destroyed. Data will be stored securely on the university’s server and files will be password protected. Only the relevant members of the research team will have access to these files. In accordance with NHMRC guidelines for clinical trials, data will be retained for 15 years and then securely destroyed. Data will be managed in accordance with the National Statement on Ethical Conduct in Human Research and the Charles Darwin University Research Data Management Procedures [45].

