**Ethical approval**

Ethical approval for the study has been granted by the Charles Darwin University Human Research Ethics Committee (ref no. H22003) and the appropriate ethical approval/governance approvals will be obtained from the early psychosis service at the study site. Potential participants will be aware that their participation is entirely voluntary and that they may withdraw from the study at any point without penalty. Participants aged <18 years will also need to provide parental/guardian consent to take part in the study. Recruitment will be conducted by a trained research assistant who is not working at the service provider in order to minimise the risk that participants may feel coerced to take part (please see “Recruitment” section for more detailed information).

The intervention will be delivered by the YPEEP participant’s regular clinician who will be responsible for recognizing, responding and reporting any distress arising from the intervention (i.e. debriefing). After each YPEEP participant has completed each session of BA, the clinician will ask them about their emotional well-being and if they have experienced any distress. If distress is experienced, the participants will have access to ongoing support through their existing clinical/support team and will be aware of how to contact this team. Approval will be sought for any modifications to the protocol from the ethics committees noted above and amendments will be made to the documentation submitted to the Australian New Zealand Clinical Trials Registry, accordingly.

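### Research assistants who collect post-randomisation outcomes are left unmasked without a stated reason, although the allocation pathway does not require them to know the arm

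*Protocol*

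**What the plan says.** All of this is in the Protocol.

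- **Masking** (Random treatment allocation and blinding). Of allocation and the data collectors, the section says: "it will not be masked to the clinicians and research assistants who will collect baseline, post-intervention, and follow-up outcome data". The statistician is the only masked role, and no reason is given for leaving the data collectors unmasked.
- **Allocation pathway** (same section). The external service tells the trial coordinator the "group allocation via text message once baseline data has been collected from consenting participants". Then: "The trial coordinator then will inform the participant and clinician of treatment allocation". Research assistants are not named as recipients.
- **Who collects data** (Data collection and management). "The trained research assistant will facilitate the data collection process".
- **Who recruits** (Ethical approval). "Recruitment will be conducted by a trained research assistant who is not working at the service provider".
- **Who treats** (Ethical approval). "The intervention will be delivered by the YPEEP participant’s regular clinician".
- **Outcomes** (Preliminary intervention effects). Depressive symptoms on the CDSS are the primary outcome: nine items, each graded 0 to 3. SANS, BPRS, GASS and WSAS are secondary. Only GASS and WSAS are described as self-report.
- **Use of the data** (Statistical analyses). A GEE over three time points with effect sizes. Between-arm t-tests at follow-up are run only if the overall GEE treatment effect is significant. All tests are at the 0.05 level.

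**The concern.** Participants and treating clinicians cannot be masked when BA plus usual care is compared with usual care alone. The assessor is then the main remaining place where knowledge of the arm can be kept out of the scores. The Protocol gives this up by an explicit statement, so it is not a detail left to an analysis plan. Masking the statistician cannot correct a score already recorded by someone who knew the arm.

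What is at stake is the preliminary efficacy estimate. If raters expect BA to help and score slightly lower in that arm, the mean difference on the CDSS, and likewise on SANS and BPRS, absorbs the expectation. More participants would not remove such a bias. The estimate is meant to feed a full trial, where it could make BA look more promising than it is.

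**Working it through.** **1. Who has to know the arm?**

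| Role | Told in the described pathway? | Needs to know for its task? |
|---|---|---|
| Trial coordinator | Yes | Yes, to pass it on |
| Participant | Yes | Yes, receives the treatment |
| Treating clinician | Yes | Yes, delivers BA |
| Research assistant | Not named | No task described for this role requires it |
| Statistician | No, masked | No |

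The unmasking of research assistants comes from the masking sentence, not from the flow of information. Treating clinicians necessarily know the arm. If they collect outcomes, as the sentence allows, a therapist could rate their own patient.

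**2. Which assessments are exposed?** Baseline data are collected before allocation is released, so baseline is not exposed. The post-intervention and 3-month assessments are.

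**3. Which outcomes are exposed?** GASS and WSAS are labelled self-report. CDSS, SANS and BPRS are not. The inclusion criteria describe a routine BPRS carried out by clinical staff, which supports reading it as rater-scored. For the CDSS the Protocol does not say who scores it, so this is an inference from the contrast.

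**4. Illustrative size.** The Protocol has no figure to reproduce here: its 60 is 2 × 30, with no effect size, SD or power behind it.

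Inputs: n = 30 per arm (Sample size) and α = 0.05 (Statistical analyses). Assumptions: two-sided test, complete data, no true effect, and a constant rater shift b in SD units favouring BA.

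- SE of the difference = √(2/30) = 0.258 SD.
- Noncentrality = b / 0.258, with 58 degrees of freedom and critical t of about 2.00.

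| b (SD) | Noncentrality | Rejection rate |
|---|---|---|
| 0 | 0 | 5.0% |
| 0.1 | 0.387 | 6.7% |
| 0.3 | 1.162 | 20.8% |
| 0.5 | 1.936 | 47.8% |

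**5. If the full trial were sized on the observed effect.** Normal approximation, 80% power, two-sided 5%: n per arm = 2 × (1.960 + 0.842)² / d² = 15.70 / d².

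- Assumed true effect d = 0.4: 15.70 / 0.16 = 98.1, so 99 per arm.
- Apparent effect d = 0.6 (0.4 plus an assumed shift of 0.2): 15.70 / 0.36 = 43.6, so 44 per arm.
- Power of 44 per arm for d = 0.4: Φ(0.4 / √(2/44) − 1.96) = Φ(−0.08), about 47%.

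**6. What does not move.** A constant shift in one arm changes that arm's mean but not its within-arm SD. The proportions for training, consent, treatment completion and follow-up completion do not depend on a masked rater.

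**The case against.** The strongest reply is that this is an openly declared choice in a pilot. The four numbered objectives are all proportions, efficacy is an additional and preliminary aim, and the sample is expressly not powered for between-group differences. That stands, and it limits the consequence. It does not remove the point, because the Protocol still plans effect sizes and tests at 0.05 and means the pilot to inform a full trial.

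Several stronger readings are tempting, and the documents do not support them.

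- *Assessor masking would be complete and cost nothing.* Participants know their arm. Under Safety considerations, researchers and clinicians check at each assessment, or at the start of each BA session, for unexpected effects of the intervention, and that question can reveal the arm.
- *No one who collects outcomes needs the allocation.* This holds for research assistants only, not for treating clinicians.
- *Every assessor is independent of the service.* The Protocol says this of the research assistant who recruits. It does not say it of all those who collect outcomes, and it gives no staff numbers, so it cannot be shown that existing staff could absorb any rating now done by clinicians.
- *The SD for the next trial is biased too.* A constant rater shift leaves the within-arm SD unchanged.
- *The trial's false-positive rate is about 21%.* That figure comes from one stand-alone t-test, full follow-up and an assumed 0.3 SD shift. The planned t-tests follow a GEE gate, and attrition is not modelled.

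**Conclusion.** The point holds as a cheap improvement, not as an error that undermines the pilot. The Protocol leaves the research assistants who collect post-intervention and follow-up outcomes unmasked, gives no reason, and describes a pathway that does not require them to know. Its wording also leaves room for treating clinicians to rate. The preliminary between-group effects on CDSS, SANS and BPRS are open to detection bias. The SD and the feasibility proportions are not shown to be affected.

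The size is unknown. The 7% to 48% range and the sizing example rest wholly on assumed shifts and show only how sensitive a comparison of 30 per arm is. The conclusion also rests on the inference that the CDSS is rater-scored. If it were completed by participants, assessor masking would matter less for the primary outcome.

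**What to change.** Amend the section on random treatment allocation and blinding, and align Safety considerations with it:

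1. The trial coordinator does not disclose allocation to the research assistants who rate CDSS, SANS and BPRS.
2. Treating clinicians do not rate these outcomes after randomisation.
3. Participants are asked before each assessment not to mention their sessions.
4. At assessments, the existing question about unexpected effects of the intervention is put after the ratings, or by someone other than the rater. The check itself is kept.
5. The assessor records any unmasking at each visit.

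It would also help to state who scores the CDSS.

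Sample size and significance level do not change. The cost is protocol wording, a line on the case report form, and keeping roles separate within the existing staff. Masking will be partial: it reduces the bias rather than removing it. Where roles cannot be separated, give the reason and state unmasked rating as a limitation of the preliminary effect estimates. The limitation now named in the Discussion concerns only the generalisability of the qualitative findings.
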